#### Exclusion criteria

Patients are excluded from the study if they are unable to provide informed consent or are ineligible to available ACT services. Furthermore, those who are not proficient in English or Mandarin, or are under the age of 21 years are excluded. Patients already engaged with ACT-related interventions or alcohol addiction programs from any other institution within Singapore are also excluded.

#### Screening and recruitment

Patients who meet the inclusion criteria are identified through clinical referrals within each participating hospital using alcoholism codes ICD-10-AM, SNOMED and ICD-9-CM codes. Each hospital’s ACT teams prioritize recruitment for those who have most frequently used ED services, with the aim to recruit up to 17 patients over six months (equating to 34 patients per year).

Four hospitals participate in the study over a four-year period (see Table 1). Recruitment of participants for each site is done yearly and staggered. Considering Singapore’s limited resources, and the existence of only one tertiary addiction centre, the study initiation dates are strategically staggered to ensure sufficient supervisory support.

**Table 1 Tab1:** Details of recruitment

Intervention Site	Date of Initiation	Date of completion	Maximum Subjects
Hospital A	August 2020	February 2024	136
Hospital B	August 2021	February 2024	102
Hospital C	August 2022	February 2024	68
Hospital D	August 2023	February 2024	34

Invitations to partake in the study are extended via phone calls, offering potential subjects a week for consideration. However, pilot data suggest a significant proportion of ARFAs are homeless and lack phone access. As such, an opportunistic recruitment approach is primarily adopted, enabling engagement with eligible patients during their hospital visits. Members of the study team approach eligible patients, extending an invitation to participate and providing necessary information, including the need for retrospective data sharing consent. The consent is obtained by either Site-Principal Investigators (PIs) or Co-Investigators (Co-Is).

To optimize participant retention and ensure complete follow-up, we have implemented strategies that emphasize flexibility and participant engagement. Regular check-ins, either by phone or text, will maintain consistent communication, while appointment schedules are tailored to participants’ availabilities. If participants discontinue or deviate from the intervention protocol, we will attempt an exit interview to gather insights and continue collecting relevant outcome data, ensuring that their contribution remains valuable and meaningful to the study.

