### Secondary hypotheses

ACT is expected to improve health outcomes compared with standard care at a 12-month follow-up.ACT is expected to be more cost-effective compared with standard care at a 12-month follow-up.

The study protocol comprises a total of 17 visits, including a follow-up at six months post-final assessment. The intervention manual and comprehensive study protocol is adhered to the Standard Protocol Items: Recommendations for Interventional Trials (SPIRIT) attached in Additional file 1 (see Additional file 1) and can be made available upon request from the authors.

Employing a before-and-after study design will facilitate measurements of ACT outcomes in ARFAs before and after its formal implementation in EDs. Changes in ARFAs’ outcomes will thereby be attributed to the ACT intervention. Previous ARFAs ED usage data serves as a control group for comparative analysis. While this design does not negate the need for randomization, it offers a more pragmatic approach that can be less resource-demanding than a randomized-controlled trial (RCT). Importantly, the study can be executed concurrently with standard ED operations.

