### Participants

#### Inclusion criteria

Patients at the study site meeting the following criteria are eligible for participation: aged 21 years or older, have recorded a minimum of two alcohol-related and five all-cause visits to an ED in the preceding 12 months, and are fluent in either English or Mandarin. Patients who discontinued ACT but have completed a minimum of three ACT visits are included, considering that significant interventions would have been implemented into their social, drinking, and medical conditions by the third visit.

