#### Trial flow and sample size

A detailed flow diagram is provided (see Fig. 2), demonstrating the progression through the multidisciplinary team-based ACT interventions, occurring parallelly to standard emergency care for ARFAs. The diagram’s numerical annotations are informed by our power analysis during the study design phase. As a real-world implementation study, our recruitment goal encompasses all patients in the ARFA program. According to past data, ARFAs utilize ED services at a mean of 30.15 visits/year, with a standard deviation (SD) of 23.47. With an expected 40% usage decrease, a standard deviation of 23 visits, 80% power, and an alpha of 0.05, we estimate a required sample size of 29 patients. Anticipating a 15% attrition rate, our target recruitment number stands at 34 patients.

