#### Primary outcome: number of ED visits

The primary outcome is the number of ED visits by ARFAs, sourced primarily from the electronic records system of the participating hospitals. A comparative analysis will be conducted between the rates of ED visits pre-intervention (12 months) and post-intervention (12 months).

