### Statistical methods

Continuous variables will be reported as mean and standard deviation using Student’s t-test. Categorical variables will be reported as frequency count and percentage using Chi-square test/Fisher’s exact test. Univariate analysis will be done to select variables for an adjusted multivariable analysis. Statistical significance will be set at P < 0.05 criteria. We will adopt imputation to address missing data.

Using complete set data analysis, cases undergoing ACT will be compared their own historical outcomes as controls. ED utilizations will be compared using the paired sample t-test or Wilcoxon Signed Rank test, the post-intervention utilization of ARFAs undergoing ACT will be compared to the pre-intervention utilization.

To adjust for potential confounders, multivariable regression analysis will be undertaken. Interactions will be tested for variables that are clinically relevant and are statistically significant. Model adequacy will be assessed through coefficients of determination (R2) and by plotting error terms against predicted values. Presence of multicollinearity will be evaluated by variance inflation factor (VIF). Should complete set analysis show efficacy, we will proceed to analyze the data using an intention-to-treat analysis.

The incremental costs of delivering the intervention will be estimated and compared to any observed cost savings from reduce usage of ED services and other health services. All analyses will be performed using R 4.2.0 (www.r-project.org) and STATA version 17.0 (StataCorp. 2017. Stata Statistical Software: Release 17.0. College Station, TX: StataCorp LLC) software.

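### No rule says where the recruiting ED visit is counted; read plainly it falls only in the 'before' year, favouring ACT by up to about one visit per patient

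*Protocol article*

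**What the plan says.** Under Screening and recruitment, the protocol article gives two routes. The first is by telephone: "Invitations to partake in the study are extended via phone calls, offering potential subjects a week for consideration". Because many of these patients are homeless and have no phone, the main route is different: "an opportunistic recruitment approach is primarily adopted, enabling engagement with eligible patients during their hospital visits".

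Under Inclusion criteria, patients must "have recorded a minimum of two alcohol-related and five all-cause visits to an ED in the preceding 12 months". The date from which those months are counted back is not given.

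Under Primary outcome, the comparison is of "rates of ED visits pre-intervention (12 months) and post-intervention (12 months"), again without start or end dates. The patients are their own controls. The text after the Secondary hypotheses says "Previous ARFAs ED usage data serves as a control group for comparative analysis", and Statistical methods says "ED utilizations will be compared using the paired sample t-test or Wilcoxon Signed Rank test".

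The Cost Analysis paragraph under Secondary outcomes sets the cost of ACT in the intervention period against savings from fewer ED attendances in the 12 months after the intervention.

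**The concern.** A patient recruited while attending the ED has, by construction, at least one ED visit at the end of the period before ACT. Nothing guarantees a matching visit in the period after it. A paired comparison of the two counts then shows a small fall even if the patient's underlying rate of attendance never changes.

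Three features make this worth settling in the plan:

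- There is no concurrent control group in which the same artefact would appear and cancel, and the article attributes changes in outcome to ACT.
- The shift is the same for each affected patient, so a larger sample does not reduce it. The standard error shrinks around a biased value. The sample size calculation asks for 34 patients, but 93 had been recruited by March 2023 and Table 1 allows many more.
- The same count feeds the cost analysis, so up to one artefactual visit per patient would be credited as a saving.

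**Working it through.** **Inputs.** From Trial flow and sample size: "ARFAs utilize ED services at a mean of 30.15 visits/year, with a standard deviation (SD) of 23.47"; expected decrease 40%; SD 23 for the calculation; power 80%; alpha 0.05; required n 29, or 34 after 15% attrition. From Preliminary results: 93 recruited. From Table 1: site maxima 136 + 102 + 68 + 34 = 340.

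**Step 1: reproduce the plan's own figure.** The planned reduction is 0.40 × 30.15 = 12.06 visits. The paired normal approximation, two-sided, is n = ((1.960 + 0.842) × 23 / 12.06)² = 28.55, rounded up to 29. This matches, so 23 is read below as the SD of the paired change.

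**Step 2: where the recruiting visit falls.** Approach and consent come before ACT begins. If the visit is an ED visit, it is pre-intervention on the ordinary meaning of the word. This holds whether the 'before' window closes at consent or at the first ACT contact, and whether the 'after' window opens at the start or the end of the six-month programme. It fails only if a rule excludes that visit or assigns it to the 'after' window. The article states neither.

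**Step 3: size of the shift.** The upper bound is one visit per patient, reached if every patient is recruited at an ED visit.

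- Share of the planning mean: 1 / 30.15 = 3.3%
- Share of the planned reduction: 1 / 12.06 = 8.3%

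A simulation of 1,000,000 patients checks this. Each has a constant personal rate and there is no treatment effect. Rates are gamma-distributed and counts Poisson, giving mean 30.15 and SD 23.47, with at least five visits needed for entry.

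- Recruiting visit counted: mean 32.49 before and 31.41 after, difference 1.08
- Recruiting visit excluded: mean 32.00 before and 31.90 after, difference 0.10

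The remaining 0.10 comes from the five-visit entry threshold, so almost all of the difference comes from how this one visit is counted.

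**Step 4: effect on the test when there is no true effect.** With a shift of one visit, s = 1 / (23/√n), and the two-sided rejection rate is Φ(−1.96 + s) + Φ(−1.96 − s).

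| n | standard error | s | two-sided error | of which in favour of ACT |
|---|---|---|---|---|
| 29 | 4.27 | 0.23 | 5.6% | 4.2% |
| 93 | 2.38 | 0.42 | 7.0% | 6.2% |
| 340 | 1.25 | 0.80 | 12.6% | 12.3% |

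The nominal values are 5% and 2.5%.

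**Step 5: a milder case.** The share recruited at an ED visit is not given. If it were half (an assumption), the average shift would be 0.5 visit and the two-sided error about 5.5% at n=93 and 6.9% at n=340.

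**The case against.** The strongest reply is that the premise is not in the text. No section says that the 'before' window runs up to enrolment or that the recruiting visit is counted in it. The look-back in the inclusion criteria is an eligibility rule, not the outcome window. How the index day is treated is a data-extraction detail that a journal article may leave to the full protocol, the data collection schedule or the timetable figure, none of which is shown. If the index day were excluded, this bias would vanish. If it were counted as the first day of the 'after' window, the bias would reverse. The main route is described as hospital visits, not ED visits, and phone recruits have no recruiting visit. At the planned size the error rate is 5.6%, close to nominal.

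Much of this stands. A reader might infer that the protocol fixes the window at enrolment and counts the visit, or that the bias must always favour ACT. The article supports neither as a stated fact. One visit per patient is a ceiling. A reader might also express the bias as one visit in five, or 20%, for a patient at the entry threshold. That is a poor guide, because the test works on differences in visits and the sites prioritise the heaviest users.

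The claim that this is only omitted detail does not stand. The article itself fixes both the recruitment route and the paired before-and-after comparison. Following those two statements in their ordinary sense puts a recruiting ED visit on one side only.

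**Conclusion.** The point holds as a small bias from windows that are not properly fixed. Where the recruiting visit is an ED visit and is counted by the ordinary meaning of the text, it favours ACT by up to about one visit per patient. That is at most 3.3% of the planning mean and 8.3% of the planned reduction. The same excess carries into the estimated cost savings.

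The error rates rest on three assumptions: SD 23 is the SD of the paired change, every patient is recruited at an ED visit, and the normal approximation applies. A lower share recruited in the ED brings them down; a smaller SD of change would push them up. The inflation is negligible at n=29 and becomes material only as recruitment approaches the Table 1 maxima.

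A reader might infer that this artefact could explain a positive result of the planned size. It could not: one visit does not make a fall of 12.06. Regression to the mean from recruiting the most frequent attenders first is a separate matter and adds nothing to the size given here.

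**What to change.** State that the recruiting ED visit is counted in neither window. The 12-month 'before' window ends the day before that visit or, for patients recruited by phone, the day before the contact date. State the start of the 'after' window as well, keeping whatever start the protocol intends. The cost paragraph separates the intervention period from the 12 months that follow it, so this correction should not move that start. Apply the same counts in the cost analysis. Report the primary result with the recruiting visit included as a sensitivity analysis. If the full protocol already excludes the visit, one sentence saying so closes the point.

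The cost is a date shift in the extraction from electronic records and one additional analysis, with no new data. The estimated reduction becomes slightly smaller, by at most about one visit per patient.

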#### Trial flow and sample size

A detailed flow diagram is provided (see Fig. 2), demonstrating the progression through the multidisciplinary team-based ACT interventions, occurring parallelly to standard emergency care for ARFAs. The diagram’s numerical annotations are informed by our power analysis during the study design phase. As a real-world implementation study, our recruitment goal encompasses all patients in the ARFA program. According to past data, ARFAs utilize ED services at a mean of 30.15 visits/year, with a standard deviation (SD) of 23.47. With an expected 40% usage decrease, a standard deviation of 23 visits, 80% power, and an alpha of 0.05, we estimate a required sample size of 29 patients. Anticipating a 15% attrition rate, our target recruitment number stands at 34 patients.

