### Preliminary results

A total of 93 ARFAs have been recruited from three participating hospitals as of March 2023 (see S Table 2): Hospital A (n = 37), Hospital B (n = 41), and Hospital C (n = 15). A broad age range was represented in the study with a median of 57 years and an Interquartile Range (IQR) of 51–64 years across all hospitals. It is noteworthy that Hospital C reported the highest median age of 61. In terms of age distribution, the majority of patients (76.34%) were below 65 years of age, and Hospital A reported the greatest proportion (86.49%) in this category.

The study cohort was predominantly male, accounting for 93.55% of the overall sample. Ethnic diversity was observed among the patients; however, Indian ethnicity was the most prevalent, making up 63.44% of the total sample.

In the context of marital status, a substantial proportion of patients were divorced (36.56%), with Hospital A having the highest prevalence of divorce (48.65%). On the contrary, Hospital C had a distinctively higher percentage of single patients (53.33%) compared to other hospitals.

The living arrangements of patients varied significantly across the three hospitals. Overall, 41.94% of patients lived in their own or a family-owned home. An outlier was observed in Hospital C, where the majority of patients (73.33%) lived in a rental flat, a considerably higher percentage than that reported by the other hospitals.

Assessing employment status revealed that a significant majority of the cohort was unemployed (66.67%), a trend consistently seen across all hospitals. Furthermore, smoking was common among the patient population, with an overall prevalence of 81.72%.

When examining medical histories, liver disease emerged as the most frequently reported condition, affecting more than half (52.69%) of the patients. A noteworthy observation was the significantly higher prevalence of substance abuse in Hospital C (60%), a finding that was statistically significant across the hospitals (p = 0.004).

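### The 29 patients for 80% power rest on an SD of change that is never justified: 23 appears to be the cross-sectional SD of annual visits, so the stated power is unsupported in either direction

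*Protocol article*

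**What the plan says.** The section on trial flow and sample size in the protocol article reports from past data that "ARFAs utilize ED services at a mean of 30.15 visits/year, with a standard deviation (SD) of 23.47". It then assumes a 40% fall and continues with "a standard deviation of 23 visits, 80% power, and an alpha of 0.05, we estimate a required sample size of 29 patients". The 23 carries no label: the text does not say whether it is the SD of annual counts or of the within-patient change. Sidedness is not stated. For losses it adds "Anticipating a 15% attrition rate, our target recruitment number stands at 34 patients".

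The primary outcome section compares 12 months before with 12 months after the intervention. In the statistical methods each patient serves as their own historical control, and "ED utilizations will be compared using the paired sample t-test or Wilcoxon Signed Rank test". Under preliminary results the article reports that "A total of 93 ARFAs have been recruited from three participating hospitals as of March 2023".

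**The concern.** A paired test gets its power from the SD of the individual before-after differences. The SD of annual visits across patients is a different quantity. The two are linked by the correlation between a patient's two yearly counts and by how the spread changes after the intervention. The article gives neither, and the SD it uses is nearly identical to the between-patient SD in the preceding sentence.

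If the cross-sectional SD was entered as the SD of change, 80% is a by-product of that substitution and does not describe the planned comparison. A reader would then take 29 completers as adequate, or 34 enrolled as the benchmark, without support for either. A smaller matter is that the normal approximation and the rounding for attrition both give slightly low numbers for the planned t-test.

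**Working it through.** **Inputs (protocol article, trial flow and sample size):** mean 30.15 visits/year; SD of annual visits 23.47; fall 40%; SD used 23; power 80%; alpha 0.05; attrition 15%. From the statistical methods: paired t-test or Wilcoxon signed rank test.

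**1. Reproducing 29.** The fall to detect is 0.40 × 30.15 = 12.06 visits. The two-sided normal approximation for paired data gives

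n = (1.960 + 0.842)² × 23² / 12.06² = 28.55, rounded up to 29.

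This matches exactly. The alternatives do not: the one-sided normal approximation gives 22.49 (23), a two-group formula with SD 23 gives 58 per group, and SD 23.47 in the paired formula gives 29.73 (30). So 23 acted as the SD of the within-patient change, with a two-sided test.

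**2. What that implies.** With equal SDs before and after, SD of change = SD × √(2(1 − ρ)), where ρ is the pre-post correlation. This equals the cross-sectional SD only when ρ = 0.5.

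**3. Power of the paired t-test at 29 completers, fall 12.06, two-sided 0.05 (noncentral t).** The article gives no ρ, so the values below are assumptions. The right-hand columns let the post-intervention SD fall by 40% as well (23.47 to 14.08), so SD of change = 23.47 × √(1 + 0.36 − 1.2ρ).

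| ρ | SD of change, equal SDs of 23.47 | Power at 29 | n for 80% | SD of change, post SD down 40% | Power at 29 | n for 80% |
|---|---|---|---|---|---|---|
| 0 | 33.19 | 47% | 62 | 27.37 | 63% | 43 |
| 0.3 | 27.77 | 62% | 44 | 23.47 | 76% | 32 |
| 0.5 | 23.47 | 76% | 32 | 20.46 | 87% | 25 |
| 0.7 | 18.18 | 93% | 20 | 16.92 | 96% | 18 |

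**4. Accepting the SD as given.** If the SD of change really is 23, paired t-test power at 29 is 77.8% (80.6% by the normal approximation), and 80% first holds at 31 (80.6%). If it is 23.47, power at 29 is 76.2% and 80% first holds at 32 (80.4%).

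**5. Attrition.** 29 / 0.85 = 34.12, which rounds up to 35; 34 × 0.85 = 28.9 completers. The same step gives 31 / 0.85 = 36.5 (37) and 32 / 0.85 = 37.6 (38).

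**6. Actual enrolment.** 93 × 0.85 = 79 completers. Paired t-test power for 12.06 visits is then 89% even at ρ = 0 with equal SDs of 23.47. The fall detectable with 80% power is about 7.3 visits (24% of 30.15) at SD of change 23, and about 10.6 visits (35%) at 33.19.

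**The case against.** The strongest reply is that the origin of 23 is inferred. The article does not label it, it condenses a longer protocol, and the flow diagram, whose numbers it says come from the power analysis, is not shown here. This stands, so the wording should be that 23 appears to be the cross-sectional SD. What does not depend on the inference is that 29 requires 23 to be the SD of change, and that nothing printed supports that value.

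Second, a reader might infer that the study was planned with too little power. The documents do not support that. At 29 completers power passes 80% once the correlation exceeds about 0.55 with equal SDs, or about 0.38 if the SD falls along with the mean, which is plausible for counts that drop by 40%. The direction of the error is unknown.

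Third, the rounding is one patient, and 29 × 1.15 = 33.35 also rounds up to 34. The step from normal to t distribution is two patients and about two percentage points. Both are minor.

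Fourth, the target is not a cap: the article aims to recruit everyone in the programme, and enrolment has far exceeded 34. This also stands and limits the practical effect.

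Two neighbouring matters should not be added to the weight of this point. Regression to the mean after selecting frequent attenders is a question of design and estimand, which no choice of SD resolves. That 34 is also one hospital's yearly recruitment aim does not make the power calculation wrong.

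**Conclusion.** The point holds as a correction to the stated sample size and power. The 29 is a two-sided normal-approximation paired figure with 23 as the SD of change. No SD of change or correlation is given to support it, and the nearest source is the between-patient SD of 23.47. Across assumed correlations of 0 to 0.7, power at 29 completers runs from 47% to 93% with equal SDs, and from 63% to 96% if the post-intervention SD falls 40%. On the article's own SD of 23, power for the planned t-test is 77.8%, so the stated 80% is slightly too high even then.

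These figures assume a fall of 12.06 visits, a two-sided 0.05 test and roughly normal differences. They do not cover the Wilcoxon alternative. The consequence is for reporting: at about 79 completers the primary comparison has ample power for the assumed fall across the whole range examined.

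**What to change.** Rewrite the sample-size paragraph as follows.

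- Label the SD as the SD of the within-patient change and give its source. If it is derived from the cross-sectional SD, state the assumed pre-post correlation and post-intervention SD.
- State that the test is two-sided and base the calculation on the t distribution.
- Show power over an SD of change of about 17 to 33. If single figures are kept, give 31 completers / 37 enrolled as conditional on an SD of change of 23, or 32 / 38 on 23.47. Neither pair is a corrected requirement, since each still rests on the unverified SD.
- Round up when allowing for attrition.
- State that enrolment already exceeds the target, and that about 79 completers from 93 enrolled can detect a fall of about 7.3 visits at SD of change 23 or 10.6 at about 33.

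The cost is one recalculation and one reworded paragraph, with no additional patients. The drawback is a stated power that is less favourable or less certain than 80%.
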